## Abstract

**Background:**

ST-elevation myocardial infarction (STEMI) accounts for nearly one third of acute coronary syndromes. Despite improved STEMI patient care, mortality remains high, contributing significantly to the ischemic heart disease burden. This may partly be related to ischemia-reperfusion injury (IRI). Remote ischemic conditioning (RIC), through short cycles of ischemia-reperfusion applied to a limb, has been shown to reduce IRI in various clinical settings. Our primary hypothesis is that RIC will reduce adverse events related to STEMI when applied as adjunctive therapy to primary percutaneous coronary intervention (PCI).

**Methods/Design:**

“Remote ischemic conditioning in ST-elevation myocardial infarction as adjuvant to primary angioplasty” (RIC-STEMI) is an ongoing prospective, single-center, open-label, randomized controlled trial to assess whether RIC as an adjunctive therapy during primary PCI in patients presenting with STEMI can improve clinical outcomes. After enrollment, participants are randomized according to a computer-generated randomization schedule, in a ratio of 1:1 to RIC or no intervention, in blocks of four individuals. RIC is begun at least 10 min before the estimated time of the first balloon inflation and its duration is 30 min. Ischemia is induced by three cycles of inflation of a blood pressure cuff placed on the left lower limb to 200 mmHg and then deflation to 0 mmHg for another 5 min. Primary endpoint is a combined endpoint of death from cardiac cause or hospitalization for heart failure (HF) on follow-up (including device implantation: implantable cardioverter defibrillator, cardiac resynchronization and left ventricular assist device). Secondary endpoints are myocardial infarction (MI) size (estimated by the 48 h area under the curve of serum troponin I levels), development of Q-wave MI, left ventricular function (assessed by echocardiography within the first 3 days after admission), contrast-induced nephropathy, in-hospital mortality, all-cause mortality and, finally, major adverse cardiovascular events. Patients will have a minimum follow-up period of 12 months. From 11 March 2013 to 31 December 2014, 324 patients have been enrolled and randomized. We expect to complete enrollment of the 494 patients deemed necessary within 3 years.

**Trial registration:**

ClinicalTrials.gov identifier: NCT02313961; registered on 8 December 2014.

**Electronic supplementary material:**

The online version of this article (doi:10.1186/s13063-015-0937-1) contains supplementary material, which is available to authorized users.

## Background

Ischemic heart disease is the leading cause of mortality worldwide, accounting for over 7 million deaths per year [1]. ST-elevation myocardial infarction (STEMI) accounts for nearly one third of acute coronary syndromes. The widespread use of timely reperfusion, particularly with primary percutaneous coronary intervention, has resulted in a significant reduction in the acute STEMI mortality, reaching approximately 5 % in recent years [2]. However, this reduction of the in-hospital mortality also led to an increase in the incidence of chronic heart failure (HF) because many patients with severely depressed left ventricular function, who would have died in the acute STEMI phase in the past, now survive at the cost of severe HF [2]. As a result, 6-month mortality associated with STEMI remains unacceptably high, approximately 12 %, with an even higher mortality rate in higher risk patients [3, 4]. Consequently, attention is no longer solely aimed at reducing the acute mortality associated with STEMI but also to limit the downstream consequence of postinfarction HF [5]. Ischemia-reperfusion injury (IRI) is believed to account for up to 40-50 % of infarct size and may be a target to prevent evolution to heart failure after STEMI [6, 7]. Several pharmacological alternatives have been attempted to prevent IRI in promising animal experiments; nevertheless, clinical translation has been disappointing [8]. On the opposite side, ischemic conditioning (IC) by short cycles of ischemia-reperfusion applied before, during or after a major ischemic event has clearly been shown to attenuate IRI in various clinical scenarios. Moreover, even so-called remote IC (RIC), which are repeated bouts of limb ischemia, are cardioprotective, [9–11]. In 2010, Bøtker et al. showed improved myocardial salvage index as assessed by single photon emission computed tomography 30 days after PCI in patients randomly assigned to receive concomitant RIC [12], whereas Rentoukas *et al*. found higher proportions of ST-segment resolution with adjunctive RIC compared with PCI alone. However, significant reductions in troponin I peaks only reached statistical significance in a subgroup undergoing both RIC and morphine therapy combined with PCI [13]. More recently, Sloth et al. evaluated the long-term effect of RIC on the population initially analyzed by Bøtker et al. (166 patients underwent PCI with adjunctive RIC and 167 patients simply underwent PCI). The authors showed improved long-term prognosis for patients that underwent adjunctive RIC as regards the composite endpoint of adverse cardiac and cerebrovascular events: all-cause mortality, MI, readmission for HF, and ischaemic stroke/transient ischaemic attack [14]. However, although very promising, their results are inconclusive with regard to cardiovascular mortality and HF development, since the study was not powered to show differences in these clinical events. Large-scale studies addressing major adverse cardiovascular events are warranted [5, 7, 15].

The primary objective of our trial is to test the hypothesis that RIC will reduce adverse events related to STEMI, mainly by preventing evolution to post-infarction HF.

## Methods/Design

The trial protocol was developed in accordance with the SPIRIT (Standard Protocol Items: Recommendations for Interventional Trials) guidelines [16] (Appendix 1). Overview of the study design

RIC-STEMI is an ongoing prospective, single-center, open-label, randomized controlled trial to assess whether RIC as an adjunctive therapy during primary PCI in patients presenting with STEMI can improve clinical outcomes as assessed by a cardiac-caused death or hospitalization for heart failure (HF) for a minimum follow-up period of 12 months. According to IRI pathophysiology, RIC is expected to reduce infarct size and, consequently, post-infarction heart failure and the adverse events associated to it. In contrast, RIC is not expected to have any major effect on further ischemic and thrombotic events; therefore, other major cardiovascular events (MACE) such as new-onset MI, stroke and need for redo revascularization, either by coronary artery bypass grafting (CABG) or PCI, are not part of the primary endpoints.

### Setting and participants

All PCI eligible patients presenting with putative STEMI at our institution are screened for enrollment. Our hospital is a tertiary referral and academic center treating almost 300 STEMI patients per year.

Inclusion criteria are indicated as follows:1.Patients ≥ 18 years old;2.STEMI defined as chest pain (or epigastric pain) for more than 30 min and either (a) new ST elevation at the J point in two contiguous leads with the cut-off points of ≥0.2 mV in men or ≥0.15 mV in women in leads V2-V3 or ≥0.1 mV in all other leads or (b) new or presumed new left bundle branch block;3.Symptom onset not more than 12 h before presentation; and4.Willingness and capability to provide informed consent.

Exclusion criteria are indicated as follows:1.Cardiogenic shock as defined by systemic hypotension (systolic arterial pressure (SAP) below 90 mmHg) and evidence of tissue hypoperfusion;2.Postcardiac arrest status;3.Need for mechanical ventilation;4.Known peripheral artery disease or evidence of lower limb ischemia; or5.Recent myocardial infarction (within 30 days).

Patients will also be excluded from further analysis if coronarography does not confirm STEMI or if CABG is required, according to the attending physician’s assessment.

### Randomization and interventions

After enrollment, participants are randomized according to a computer-generated randomization schedule, in a ratio of 1:1 to RIC or no intervention, in blocks of four individuals.

After the patient’s arrival in the catheterization laboratory (cath lab), a blood pressure cuff is placed on the left lower limb by one of the cath lab nurses. Because more than 95 % of our patients are catheterized using the radial artery, the left lower limb was chosen in order to not interfere with this approach. RIC is begun approximately 10 min before the estimated time of the first balloon inflation and its duration is 30 min. As reperfusion must be achieved as early as possible, RIC may be completed during and even after the angioplasty. Ischemia is induced by three cycles of inflation of the blood pressure cuff to 200 mmHg and then deflation to 0 mmHg for another 5 min (Appendix 2). Apart from temporary moderate pain in the treated thigh, RIC has been shown to be innocuous. All patients receive the standard of care therapy according to institutional guidelines, namely treatment with 250 mg aspirin intravenously, a P2Y_12_ inhibitor orally and 5000 IU unfractioned heparin intravenously before PCI. The choice of balloons, stent types and PCI procedure, as well as the use of glycoprotein IIb/IIIa inhibitors, is left to the discretion of the attending physician.

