### Sample size

Sample size for the survival analysis was computed with the aid of IBM SPSS Sample-Power software with two-tailed type I error rate set at 0.05 and power at 0.80, conservatively admitting 5 % drop-outs during the RIC protocol and 5 % losses to follow-up. Considering an accrual period of 36 months, a minimum follow-up period of 12 months (maximum follow-up of 48 months), overall primary combined endpoint incidence of 14 % (data from our institution) and a treatment effect of 40 % (arbitrarily set as clinically relevant), we estimate we will need to enroll 224 patients per group (total of 448). Nevertheless, since 8 % of initially enrolled patients (data from our institution) will have unconfirmed STEMI, we will need to enroll 22 more patients per group (246) for a total of 492 patients.

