### Ethics

This study is being conducted in accordance with the Declaration of Helsinki 1964 as revised in 2013 and the International Conference of Harmonisation Guidelines for Good Clinical Practice.

Considering that STEMI is a medical emergency, little time is available. Eligible patients are orally informed and asked to participate in the study. Enrollment will be based on witnessed oral consent, and full written informed consent will be obtained by one of the investigators only after the acute phase has been addressed. Patients are notified at enrollment of their freedom to abandon the study at any time without consequences.

The study protocol (version HB-CARD-01; 20/11/2012) has been reviewed and approved by our Institution’s Ethical Committee (“Comissão de Ética para a Saúde do Hospital de Braga”), as verified with the board approval number 94/2012 (submitted and approved).

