## Trial status

RIC-STEMI is still recruiting participants.

From 11 March 2013 to 31 December 2014, 324 patients were enrolled and randomized for RIC-STEMI, but 29 of those were excluded from further analysis because STEMI was not confirmed on coronarography.

RIC was well tolerated by an overwhelming majority of patients.

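### A single published block size of four in an open-label, single-centre trial lets up to one third of allocations be known in advance by staff who follow the sequence

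*Protocol article*

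**What the plan says.** The section Randomization and interventions states: "After enrollment, participants are randomized according to a computer-generated randomization schedule", and then "in a ratio of 1:1 to RIC or no intervention, in blocks of four individuals". The abstract repeats this. One block size is given. Neither a second or random size nor a stratification factor is named.

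The overview in Methods/Design describes the setting: "RIC-STEMI is an ongoing prospective, single-center, open-label, randomized controlled trial". The comparator is no intervention and no sham inflation is described. For the active procedure, "a blood pressure cuff is placed on the left lower limb by one of the cath lab nurses". Recruitment forms one stream: "All PCI eligible patients presenting with putative STEMI at our institution are screened for enrollment" (Setting and participants).

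On consent, the Ethics section relies first on witnessed oral agreement, and "full written informed consent will be obtained by one of the investigators only after the acute phase has been addressed".

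On numbers, the Sample size section says "we will need to enroll 22 more patients per group (246) for a total of 492 patients", and Trial status reports: "From 11 March 2013 to 31 December 2014, 324 patients were enrolled and randomized for RIC-STEMI". Trial status also says that recruitment was still open.

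**The concern.** With a constant block size, the last place in every block is determined by the earlier ones, and sometimes the last two are. Hiding the list does not help if earlier allocations can be seen and the size is known. Here an inflated cuff shows the arm to those in the catheterisation laboratory, one site appears to use one sequence, and the size is in print while patients are still being enrolled.

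Staff who foresee the next arm could, even without intending to, be more or less ready to offer the study to a particular patient. The groups would then differ before treatment starts. Intention-to-treat analysis does not undo selection that precedes randomisation. The blinded assignment of cause of death and blinded data review (Study endpoints) protect outcome assessment, not entry.

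**Working it through.** The article gives no predictability figure, so there is none to reproduce.

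**Inputs.** Ratio 1:1 and block size 4 (Randomization and interventions); 492 patients planned (Sample size); 324 randomised from 11 March 2013 to 31 December 2014 (Trial status).

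**Step 1: certain allocations.** A block holds two RIC (R) and two control (C) places, giving C(4,2) = 6 equally likely orders. A place is certain once one arm is used up.

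| Order | Certain places | Count |
|---|---|---|
| RRCC | 3, 4 | 2 |
| CCRR | 3, 4 | 2 |
| RCRC | 4 | 1 |
| RCCR | 4 | 1 |
| CRRC | 4 | 1 |
| CRCR | 4 | 1 |

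Expected number per block = (2×2 + 4×1)/6 = 4/3. Share = (4/3)/4 = 33.3%. By position: 0%, 0%, 33.3%, 100%.

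**Step 2: best guess.** Always guess the arm with more places left. The chance of being right is 1/2 at place 1 and 2/3 at place 2. At place 3 it is (1/3)×1 + (2/3)×(1/2) = 2/3, and at place 4 it is 1. The sum is 2.833, and 2.833/4 = 70.8%.

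**Step 3: patients affected.**
- Already randomised: 324/4 = 81 complete blocks; 81 × 4/3 = 108.
- Remaining: 492 − 324 = 168; 168/3 = 56.
- Using the abstract's total of 494 instead: 170 remaining; 170/3 ≈ 57.

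These counts are ceilings. They assume an observer who knows the size and every earlier allocation in order. Patients later excluded because STEMI was not confirmed (29 of 324) still use their place in the block.

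**Step 4: can the sequence be followed?** 324 patients in about 661 days is one every 661/324 ≈ 2 days, so a block closes in about 8 days.

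**Step 5: effect of varying the size.** For sizes 4, 6 and 8 chosen with equal probability, guessing the arm used less so far needs no knowledge of the current size. Expected correct guesses per block are 2.833, 4.1 and 5.329, so success = (2.833 + 4.1 + 5.329)/18 = 68.1%. A simulation of 300 trials of 492 patients gave the certain share; the observer knew the possible sizes and all past allocations, but not the current block's size.

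| Scheme | Certain | Best guess |
|---|---|---|
| Fixed 4 | 33.3% | 70.8% |
| Fixed 6, known | 25.0% | 68.3% |
| Fixed 8, known | 20.0% | 66.6% |
| Random 4/6 | about 5.4% | about 69.3% |
| Random 4/6/8 | about 2.3% | about 68.1% |

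For the remaining 168 patients, 4/6/8 would mean about 0.023 × 168 ≈ 4 certain allocations in place of up to 56.

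**The case against.** The strongest reply is that predictability is conditional. The article does not say who enrols, who holds the schedule, or what enrolling staff know of the block size. A nurse places the cuff and an investigator takes written consent, so several people are involved, in emergencies and presumably across shifts. Someone present sees one allocation; nobody is shown to have followed all 324. This stands, and it is why 33.3% and 56 are upper bounds.

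Room for steering is also limited. Most entry criteria are objective: ECG thresholds, duration of pain, time from onset, ventilation, recent infarction. Suspected STEMI describes who is screened and is not itself an entry criterion, and hypoperfusion counts only together with low systolic pressure. This largely stands. What remains is discretion in approaching a patient and in judging willingness and capacity to consent. At almost 300 STEMI patients a year (Setting and participants), about 300 × 661/365 ≈ 543 would have presented while 324 were randomised, or about 60%. That assumes the full 300 a year, and many of the others will have been properly ineligible. It shows that not everyone enters, not that anyone was selected.

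Small blocks also keep the arms balanced over calendar time in a long accrual. That is true, but varying blocks of up to eight give nearly the same protection. Finally, 324 of 492 patients (66%) were already randomised, so a new list reaches at most the last third.

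**Conclusion.** The point holds as a design weakness with a cheap remedy. Fixed blocks of four, known to staff who can see past allocations, make up to 33.3% of allocations certain and allow 70.8% best-guess success. Up to about 56 of the remaining 168 patients are affected. The figures rest on enrolling staff knowing the size and tracking the sequence, and on there being one unstratified list, which is inferred because no stratification factor is named.

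Four stronger readings are tempting and not supported:

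- **That allocations were in fact foreseen, or that bias occurred.** Nothing in the article shows this.
- **That concealment was absent.** A condensed article may leave the mechanism to the full protocol, and the point does not depend on it.
- **That the risk compounds with the exclusions after randomisation** (STEMI not confirmed, or bypass surgery required). Those decisions are made after allocation in an open-label trial and are equally exposed under any block size.
- **That random sizes cut guessing below what larger fixed blocks achieve.** At 68.1%, sizes 4/6/8 are practically level with fixed blocks of six (68.3%) and worse than fixed blocks of eight (66.6%). The gain lies in removing almost all certain allocations.

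**What to change.** 1. From the next block boundary, replace the current list with a new computer-generated one with randomly varying block sizes (for example 4, 6 and 8), not disclosed to enrolling staff. The 324 patients on 31 December 2014 make exactly 81 blocks; if enrolment has moved on, complete the current block first.
2. For the first 324 patients, report baseline characteristics by arm and position within block, including those later excluded so that positions stay correct. An arm difference concentrated at places 3 and 4 would point to selection. Its absence would be reassuring but not proof, because each position holds only 81 patients.

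The cost is a new list, a short amendment and one descriptive table from existing data. If recruitment stops inside a block of eight, the arms can differ by at most 4 patients, which is negligible against 246 per group. The change cannot repair entry for patients already randomised, and it lowers best-guess success only from 70.8% to about 68%.

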### Study endpoints

RIC is expected to reduce myocardial damage associated with IRI, preventing postinfarction heart failure.

The primary endpoint is a combined outcome of death from cardiac cause or hospitalization for HF on follow-up (including device implantation: implantable cardioverter defibrillator, cardiac resynchronization and left ventricular assist device). Secondary endpoints are myocardial infarction (MI) size (estimated by the 48 h area under the curve of serum troponin I levels), development of Q-wave MI, left ventricular function (assessed by echocardiography within the first 3 days after admission), contrast-induced nephropathy, in-hospital mortality, all-cause mortality and, finally, MACE on follow-up.

Patients will have a minimum follow-up of 12 months. Information will be obtained through medical record consultation and phone calls. Cardiac and noncardiac causes of death will be assigned by three consulting cardiologists who will not know which patients were submitted to RIC. Data will be reviewed by two independents researchers who also will not know which patients were submitted to RIC.

### Sample size

Sample size for the survival analysis was computed with the aid of IBM SPSS Sample-Power software with two-tailed type I error rate set at 0.05 and power at 0.80, conservatively admitting 5 % drop-outs during the RIC protocol and 5 % losses to follow-up. Considering an accrual period of 36 months, a minimum follow-up period of 12 months (maximum follow-up of 48 months), overall primary combined endpoint incidence of 14 % (data from our institution) and a treatment effect of 40 % (arbitrarily set as clinically relevant), we estimate we will need to enroll 224 patients per group (total of 448). Nevertheless, since 8 % of initially enrolled patients (data from our institution) will have unconfirmed STEMI, we will need to enroll 22 more patients per group (246) for a total of 492 patients.

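### The enrolment target is 494 in the Abstract and 492 in Sample size, and the stated 8 % unconfirmed-STEMI rate gives 20 extra patients per group, not 22

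*Protocol article*

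**What the plan says.** The Sample size section of the protocol article first gives a requirement before any allowance for unconfirmed STEMI: "we estimate we will need to enroll 224 patients per group (total of 448". The design inputs are "two-tailed type I error rate set at 0.05 and power at 0.80", an "overall primary combined endpoint incidence of 14 % (data from our institution"), a 40 % treatment effect, 36 months of accrual and at least 12 months of follow-up. The 224 already includes an attrition allowance: "conservatively admitting 5 % drop-outs during the RIC protocol and 5 % losses to follow-up".

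A second allowance follows, for patients enrolled on suspicion whose STEMI is then not confirmed: "since 8 % of initially enrolled patients (data from our institution) will have unconfirmed STEMI". From this the section concludes "we will need to enroll 22 more patients per group (246) for a total of 492 patients".

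The Methods/Design paragraph of the Abstract states the total differently: "We expect to complete enrollment of the 494 patients deemed necessary within 3 years".

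Trial status reports experience to the end of 2014: "324 patients were enrolled and randomized for RIC-STEMI, but 29 of those were excluded from further analysis". The reason given for those exclusions is that STEMI was not confirmed on coronarography.

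**The concern.** Two separate things do not fit.

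- **Two totals.** The Abstract and the Sample size section describe the same requirement, both are current text, and they differ by two patients. At least one is wrong, and a reader cannot tell which is intended.
- **The increment.** The allowance is a single division whose inputs and result are all printed, so it should reproduce exactly. It does not: the stated rate leads to 20 extra patients per group, and 22 are printed.

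What is at stake is traceability. Enrolment was still open when the article was written, and the final report will be compared with the planned number. That number should be the same everywhere and should follow from its stated inputs.

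**Working it through.** **Inputs.** From Sample size: 224 per group (448 in total), 8 % of enrolled patients unconfirmed, 22 added per group, 246 per group, 492 in total. From the Abstract: 494. From Trial status: 29 of 324.

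**The plan's own sum.** 224 + 22 = 246 and 2 × 246 = 492. The addition is right, so the question is whether 8 % yields 22.

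**The stated rate.** The 8 % is a share of those enrolled, so the number to enrol is N/(1 − d):

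- Per group: 224/(1 − 0.08) = 243.5, rounded up to 244. That is 20 more per group and 488 in total.
- On the total: 448/0.92 = 486.96, rounded up to 487.
- Multiplying instead of dividing: 224 × 1.08 = 241.9, rounded up to 242, or 484 in total.

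No version gives 246 or 247 per group.

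**The rate implied by 22.** 22/246 = 8.9 % of those enrolled.

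**Rates that would give the printed totals.**

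| Calculation | Per group | Total, rounded to nearest | Total, rounded up |
|---|---|---|---|
| 224/0.92 (stated 8 %) | 243.5 | – | 488 |
| 224/0.91 (9 %, by division) | 246.15 | 492 | 494 |
| 224 × 1.10 (10 %, by multiplication) | 246.4 | 492 | 494 |

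A rate near 9 % with two rounding conventions would therefore give both printed totals. The third row shows that this is not the only possible route, so the origin of the 22 cannot be settled from the article.

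**Size.** 492 − 488 = 4 (0.8 %); 494 − 488 = 6 (1.2 %); 494 − 492 = 2 (0.4 %).

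**Effect at the stated 8 %.** 246 × 0.92 = 226.3 and 247 × 0.92 = 227.2 confirmed patients per group. Both exceed 224.

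**The base of 224.** This is not in dispute. As a plausibility check, assume that 14 % is the 12-month incidence averaged over both arms (the time point is not stated), that the 40 % effect is a hazard ratio of 0.60, and that survival is exponential with uniform accrual. The average event probability is then 0.306. The events required are 121 (Schoenfeld) or 126 (Freedman). This gives 121/0.306/2 ≈ 198 or 126/0.306/2 ≈ 206 per group, and about 219 to 229 after 5 % + 5 % losses. The stated 224 lies inside that range. Reading 14 % as the control-arm 12-month incidence gives about 264 to 275 instead, but the present point does not depend on which reading is right.

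**The case against.** The strongest reply is that nothing is harmed. Both totals lie within about 1 % of the exact figure, both are on the safe side, and a gap of 4 to 6 patients could be no more than a rounded rate. That stands as a judgement of size, and it is why the point is minor. It does not remove the contradiction between 494 and 492, and it does not make the printed 8 % yield the printed 22.

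A reader might infer more than this. The article does not support these stronger readings:

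- **That the trial is underpowered.** At the stated 8 %, both totals deliver more than 224 confirmed patients per group.
- **That 492 is correct and 494 wrong, because of blocks of four.** 492 is 123 complete blocks and 494 is 123.5, but a total need not be a multiple of the block size. Rounding 224/0.91 up gives 494.
- **That the planning rate should be replaced by the observed one.** 29/324 = 8.95 % is close to the implied 8.9 %. However, the 8 % is attributed to institutional data and the protocol version cited under Ethics is dated 20/11/2012, whereas the 29 exclusions arose in this trial from March 2013. The match does not show where 22 came from, and using it would present trial data as a design input.
- **That no margin is left for CABG exclusions.** Setting and participants does provide for them, but no CABG rate is given, and Trial status attributes all 29 exclusions to unconfirmed STEMI. A shortfall cannot be shown.
- **That the target is a stopping rule.** Both places describe a number needed, and neither defines when the trial stops.

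**Conclusion.** The point holds as a minor inconsistency with two parts. The Abstract and the Sample size section contradict each other by 2 patients. The stated 8 % leads to 244 per group and 488 in total, so the printed 22 per group corresponds to about 9 %.

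This rests on two readings of the text: that the 8 % is a share of enrolled patients, as the section words it, and that 224 is the number of confirmed patients needed per group, with the two 5 % allowances already inside it. Multiplying instead of dividing moves further from the printed figures (484), so the mismatch does not hinge on that choice. Which total the sponsor intended cannot be determined from the article.

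**What to change.** State one total in both the Abstract and the Sample size section, and show the calculation with the exclusion rate and the rounding rule. Either of these would do:

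1. Keep 8 %: 224/0.92 = 243.5, so 244 per group and 488 in total. If 492 remains the target, say that it includes a margin of 4 patients.
2. If the planning rate actually used was nearer 9 %, state it with its pre-trial source: 224/0.91 = 246.15 per group. Rounding to nearest gives 246 and 492; rounding up gives 247 and 494. Print whichever follows from the rule chosen.

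The choice belongs to the sponsor, who knows which rate was used. The cost is a text correction in two places, with no extra patients and no change to the design.
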